#### Control intervention

Those in the control group will receive the follow up as usual including psychiatrist or physician consultation.

### Outcomes measures

As primary endpoints, we will assess the number of patients who will reattempt suicide in each group at month 6.

As secondary endpoints, we will assess the number of patients who will reattempt suicide at month 13, the number of suicide attempts in the intervention and control groups at month 6 and 13, and the number of deaths by suicide in the intervention and control groups at 6 and 13 month. In both group, suicidal ideations will be assessed at the baseline, 6 and 13-months. Medical costs and satisfaction will be assessed at month 13.

Baseline evaluation will be done in ED or PU before discharge. Socio-demographic details, including age, gender, employment, educational status, history of suicide attempt, country of birth, medical history and details of any treatment being received, will be recorded on a specifically designed, standardized questionnaire.

The Columbia Scale measures suicidal ideation and intent. It is a 25 item screening scale with items including binary variables (yes or no) and variables scales for each question. [12]. It is also available in French.

Axis-I psychiatric diagnoses will be assessed using the International Neuropsychiatric Interview (M.I.N.I.). It is a short, structured diagnostic interview developed for DSM-IV and ICD-10 psychiatric disorders [13]. With an administration time of approximately 15 minutes, it is the structured psychiatric interview of choice for psychiatric evaluation and outcome tracking in clinical psychopharmacology trials and epidemiological studies. It has been validated in French [14].

The medico-economic questionnaire (MEDEC) is a use of care services inventory including binary variables. It is carried out by the method validated by Beecham & Knapp at 13 month [15].

The satisfaction questionnaire was designed by our team [10] to assess whether such outreach system was accepted by the patients. The subjective system effectiveness will be explored to assess patients’ acceptability.

### Sample size calculation: effect size and statistical power

Expected reattempt rate is about 18% [6,16]. We hope to reduce this rate to 9% in the intervention group. Such a reduction in reattempts with a statistical power of 0.8, requires a sample size of 247 patients in each group. Taking into account the expected proportion of SAs that will not respond to the follow-up message, 530 patients in total will be recruited.

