## Background

The construction of effective suicide-prevention and continuity of care strategies is a major challenge in the assessment and management of suicide attempters (SAs). Post-crisis management of suicidal patients varies from hospital discharge to forced hospitalization. Hospitalization rate after suicide attempt varies from 25 to 50% [1]. Fourteen to 25% of SAs treated at an emergency department (ED) reattempt suicide within the 1–2 years following discharge [2,3].

Outreach monitoring interventions via mail or phone facilitate access to care in case of recurrence in post-acute crisis patients discharged from the ED. Several studies on outreach interventions for suicidal patients have been published since 2001. The pioneer intervention was proposed by Motto et al. [4] and was based on postal contact. They proposed a follow-up in fifteen years after having started the inclusions in 1969. The objective of the postal contact was to show the patient that someone was concerned about his or her situation and maintain positive feelings towards him or her. After 5 years, a significant decrease in suicide related deaths was observed in the contacted group (versus no-contact group) of high-risk patients who refused on-going treatment. Carter et al. [5] programmed automated sent postcards. In the year following the suicide attempt, the authors reported a lower number of relapse in the contacted group, especially among women.

These positive results led to other studies exploring the effectiveness of telephone outreach (Vaiva et al. [6]). The telephone contact at one month proved, in per protocol analysis, to reduce the number of suicidal reattempts by about half over the course of one year (12% versus 21.6% in the control group). The post-hoc analysis showed no effect of the contact in first-attempters. The proposal of telephone contact was very well accepted and positively perceived by the population of this study.

In the EDGE project, a hotline was available to participants 24 hours a day, 7 days a week [7]. In the intervention group, suicide attempters repeaters rate did not differ significantly from that in the control group (15.1% vs. 17.3% at one year, 21.2% vs. 22.8% at two years). However, there was a lower number of reattempts in intervention group among suicide attempters repeaters (incidence risk ratio 0.55 at one year, and 0.49 at two years).

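### The 18% control rate that sizes the trial has no stated window and is not supported for a 6-month primary endpoint; if it is a one-year rate, power falls below 80%

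*Protocol article*

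**What the plan says.** Under Outcomes measures the primary endpoint is fixed at six months: "we will assess the number of patients who will reattempt suicide in each group at month 6".

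The sample size section starts from this: "Expected reattempt rate is about 18% [6,16]. We hope to reduce this rate to 9% in the intervention group". It says that such a reduction, "with a statistical power of 0.8, requires a sample size of 247 patients in each group". After an allowance for non-response, "530 patients in total will be recruited". The section attaches no time window to the 18% and states neither the significance level nor the sidedness. Statistical methods adds one interim analysis and a final level of 4.8%.

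The Background reports these reattempt rates with a window:

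- Telephone trial (reference 6, also a source for the 18%): contact was found, per protocol, to "reduce the number of suicidal reattempts by about half over the course of one year (12% versus 21.6% in the control group").
- Hotline trial (reference 7): the rate of repeaters "did not differ significantly from that in the control group (15.1% vs. 17.3% at one year, 21.2% vs. 22.8% at two years").
- Emergency department attempters in general (references 2 and 3): 14% to 25% within one to two years.

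The article gives no 6-month rate, and it reports neither a rate nor a window for reference 16, the second source for the 18%.

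**The concern.** A planning rate has to belong to the same window as the endpoint. The 18% lies between the two one-year control rates in the Background (17.3% and 21.6%), while the endpoint it sizes closes at month 6. If the 18% was carried over from one-year follow-up, fewer control patients will have reattempted by month 6. The same halving is then a smaller absolute difference, and 247 per arm has less than 80% power to detect it.

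What is at stake is how a null result would be read. A non-significant month-6 comparison would be judged against a claimed 80% power and could be taken as good evidence that the messages do not work. If the true power were nearer 50%, it would be weak evidence of that.

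**Working it through.** **Inputs.** From the sample size section: 18% and 9%, power 0.80, 247 per arm, 530 in total. From Statistical methods: final level 4.8%. From the Background: 21.6% at one year (reference 6 controls); 17.3% at one year and 22.8% at two years (reference 7 controls). Assumed: two-sided testing, a 5% level in the original calculation, and a true relative risk of 0.5 throughout.

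**Step 1: reproduce the 247.** With p1 = 0.18, p2 = 0.09, mean 0.135 and difference d = 0.09:

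n = [1.960 × √(2 × 0.135 × 0.865) + 0.842 × √(0.18 × 0.82 + 0.09 × 0.91)]² / 0.09² = 225.1

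With continuity correction: n′ = (n/4) × [1 + √(1 + 4/(n × d))]² = 56.28 × [1 + √(1 + 4/20.26)]² = 246.8, so 247 per arm. This matches the stated figure.

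**Step 2: could 18% be a 6-month rate, judged from the article alone?** Against reference 6, 18/21.6 = 83% of the one-year control reattempters would have to reattempt in the first half-year. Against reference 7, 18% at six months already exceeds the 17.3% seen at one year. So 18% at six months is possible on the first source and does not fit the second.

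**Step 3: candidate 6-month control rates.**

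- 18% at one year, constant hazard: 1 − (1 − 0.18)^0.5 = 9.4%.
- 18% at one year, two thirds by month 6: 12%.
- 18% at one year, 75% by month 6: 13.5%. Reference 7 has a similar share, one level up: 17.3/22.8 = 76% of two-year control reattempters fall in year one.
- 21.6% at one year (reference 6), 75% by month 6: 0.75 × 21.6% = 16.2%.

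**Step 4: power at 247 per arm and a two-sided 4.8% level (z = 1.977).** Let SE0 be the standard error under no difference and SE1 under the alternative. Power = Φ[(d − c − 1.977 × SE0)/SE1], with c = 1/247 = 0.0040 for the corrected version and c = 0 for the uncorrected one.

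Example, 9.4% against 4.7% (unrounded inputs): d = 0.0472, SE0 = 0.0231, SE1 = 0.0230. Corrected: (0.0472 − 0.0040 − 0.0457)/0.0230 = −0.107, power 46%. Uncorrected: (0.0472 − 0.0457)/0.0230 = 0.069, power 53%.

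| 6-month control rate | Halved rate | Power, corrected | Power, uncorrected |
|---|---|---|---|
| 9.4% | 4.7% | 46% | 53% |
| 12% | 6% | 58% | 64% |
| 13.5% | 6.75% | 64% | 70% |
| 16.2% | 8.1% | 74% | 78% |
| 18% | 9% | 80% | 83% |

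The corrected column is the like-for-like comparison, because that version reproduces 247. On that basis power is about 80% only if the 6-month control rate is itself about 18%.

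**The case against.** A reader might infer that the trial simply does not have 80% power. The documents do not support that. The article never calls the 18% a one-year rate. It equals neither one-year control rate in the Background, and at 83% of reference 6's 21.6% it could be a shorter-window figure. Reference 16 may contain a 6-month rate. This part of the objection stands: the shortfall is conditional.

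Its size also depends on the anchor. The three lower rows of power all take 18% as the one-year rate. Starting from reference 6's 21.6% with 75% of events by month 6, power is 74%/78% at 247 per arm and 77%/81% if all 265 per arm (530/2) are analysed. The documents offer nothing in favour of a constant hazard, and reference 7's figures point to front-loading, at least between years. This stands too, and it is why the range runs up to 78%. It does not remove the problem: at 247 per arm, every scenario below 18% falls short.

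A reader might also infer a calculation error; there is none, as step 1 shows. Nor do the documents show that the assumed halving or the non-response allowance is an error. The article describes the telephone effect as roughly a halving and presents its own target as a hope. It also makes an explicit allowance (530 recruited against 2 × 247 = 494 needed).

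Finally, it may be said that an article can leave the derivation of a planning rate to the full protocol. But this article does state the rate and its sources, and the one source whose figures it reports is given at one year.

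**Conclusion.** The point holds in conditional form. The control rate that fixes the sample size carries no window, and nothing reported in the article supports it for a month-6 endpoint. If 18% is a one-year rate, the stated 80% power is not delivered: it would be 46% to 70% for 6-month control rates of 9.4% to 13.5%. Allowing also for the higher one-year rate in reference 6, the plausible range is about 45% to 78%. These figures assume a true halving, 247 analysed per arm and a two-sided 4.8% final level. The share of reattempts before month 6 is an assumption, since the documents give none. If reference 16 does support about 18% at six months, the stated power stands and only the missing window needs correcting.

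**What to change.** In the sample size section, replace the unqualified 18% with an explicit 6-month control rate and name its source. Restate the power of the planned 530 patients at that rate, using the 4.8% final level and giving the sidedness and whether a continuity correction is used. If no 6-month source exists, say so and show power over a range of rates, as in the table above.

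Keep the month-6 primary endpoint. It matches the six-month messaging period, and month-13 reattempt and time to reattempt are already planned as supporting analyses. No additional enrolment or data collection is needed. The cost is a rewritten paragraph and, probably, a less favourable stated power.

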### Randomisation/intervention

Random allocation to the intervention group and the control group will be carried out by an independent statistician and will be stratified by center study using blocked randomization and computer generated random numbers. This will be conducted using an online randomization system. This will be concealed from the research team (psychiatrist, nurse). The statistician will notify the study coordinator regarding the group allocation. Text messages will be sent by SIAM program, designed for the pilot study. Once the patient data is entered, the program will generate four independent text messages containing patient’s name, doctor's name and monitoring schedule from the date of inclusion. At any time the patient data, date of sending the text message and message content could be modified. At any time, sending messages (transmissions) could be interrupted. The number displayed on the recipient’s mobile phone was the psychiatric ED.

### Statistical methods

Continuous variables will be summarized using mean, standard deviation, median and inter-quartile range (IQR). Categorical variables will be summarized using frequency, percentage and 95% CI. Means will be compared between the intervention and control groups using the Student test (t-test) or Mann–Whitney test. Comparisons of proportions between groups will be performed using the Chi square test or Fisher’s exact test as appropriate.

Generalized linear model will be used to compare the intervention and control groups for each outcome measure over time (baseline, 6 months, 13 months). The corresponding baseline values of each outcome measure will be used as a covariate. In addition, the effects of other possible predictors (such as gender and age) on outcome will be explored.

Analysis of predictive factors of suicide attempt repetition will be performed using logistic regressions. An approach by a decisional tree (CHAID) will also be considered. Analysis of time delay of SA repetition will be performed using conventional methods of survival analysis: Kaplan-Meyer method, log-rank test and Cox model for multifactorial models. The research for specific profiles will be conducted using classification methods to identify clusters with atypical profiles.

An interim analysis will be conducted on the first 250 participants using the O’Brian and Fleming method. If the difference between intervention and control groups is not significant (p <0.5%), statistical significance will have to reach a level of p < 4.8% by the end of the study to demonstrate a significant difference. A Data and Safety Monitoring Board (DSMB) will conduct this assessment.

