### Participants

Inclusion criteria are: male or female, aged 18 or older, surviving a suicide attempt, discharged from ED or Psychiatric Units (PU), hospitalized for less than 7 days, giving consent, and able to be contacted by phone.

The exclusion criteria are: refusing to participate, underage, incarcerated, under guardianship, without a mobile phone, enrolled in other trials, and in emergency situations where their state of health did not allow obtaining written consent.

In the case of discharge, a follow-up visit or planned hospitalization will be scheduled.

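### The longitudinal model uses baseline both as a response time point and as a covariate; this mainly concerns suicidal ideation, and the distortion depends on an arm contrast the text does not name

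*Protocol article*

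**What the plan says.** The statistical methods section of the protocol article gives the model in two consecutive sentences. A generalized linear model is to compare the arms "for each outcome measure over time (baseline, 6 months, 13 months). The corresponding baseline values of each outcome measure will be used as a covariate". Neither sentence names a random effect, a working correlation, a robust variance or the arm contrast to be tested. Independence of visits is not stated either.

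The outcome section shows which endpoints could fit this rule. For ideation it says "In both group, suicidal ideations will be assessed at the baseline, 6 and 13-months". No other outcome is said to be measured at all three times. Attempt counts are given as "the number of suicide attempts in the intervention and control groups at month 6 and 13", and costs and satisfaction are assessed at month 13 only. Every participant enters after an attempt, since the inclusion criteria require "male or female, aged 18 or older, surviving a suicide attempt".

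The primary endpoint is a proportion at one time: "As primary endpoints, we will assess the number of patients who will reattempt suicide in each group at month 6". A separate sentence provides for it: "Comparisons of proportions between groups will be performed using the Chi square test", or Fisher's exact test.

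**The concern.** Baseline can be one of the repeated responses or a covariate. When the same value is both, the baseline row has the same number on each side of the equation. It then carries no information on treatment, yet it still enters the fit. Depending on the contrast, it either pulls the arm effect towards zero or removes the benefit of the baseline adjustment.

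Two further matters come from the same sentences. A generalized linear model does not by itself allow for two or three records from one patient. And the rule is said to cover every outcome measure, although most of them have no baseline value that varies between patients.

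At stake are the size and the precision of the reported effect on suicidal ideation, and freedom to choose after the data are seen among readings that give different answers.

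**Working it through.** **The plan's own figure.** The article gives no figure for the longitudinal model. Its sample size can be reproduced, which shows what that size rests on. For 18% versus 9%, power 0.80 and two-sided 5% (assumed; the sample size section states no alpha):

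- n = [1.960 × √(2 × 0.135 × 0.865) + 0.842 × √(0.18 × 0.82 + 0.09 × 0.91)]² / 0.09² = 225.1, or 226 per group.
- With continuity correction: (225.1/4) × [1 + √(1 + 4/(225.1 × 0.09))]² = 246.9, or 247 per group, as stated.

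The sample size therefore rests on a comparison of two proportions, not on the longitudinal model.

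**Assumptions for the model check.** A continuous score with SD 1, 247 per arm, the same correlation ρ between any two visits, and a true effect of 0.25 SD at both months 6 and 13. The documents give none of these except the 247, so ρ is taken from 0.3 to 0.85.

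**Reading A: one arm effect averaged over the three visits.** All visits share the same arm and baseline columns, so each fitted coefficient is the average of the coefficients from the separate visits. At baseline, the response equals the covariate, so its coefficient is 1 and the arm coefficient is exactly 0.

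- Estimate: (0 + 0.25 + 0.25)/3 = 0.167. Follow-up visits only: (0.25 + 0.25)/2 = 0.25. The ratio is 2/3.
- A simulation (4,000 runs per setting) gave 0.166 to 0.168.
- With variance clustered on patient, type I error was 5.1% to 5.4%, but the estimate stayed at two thirds. The robust standard error shrinks by the same factor, so power is unchanged (96.5% with or without the baseline row at ρ = 0.3). The harm here is a misstated effect size.

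**Reading A with rows treated as independent.** The common baseline slope is b = (1 + 2ρ)/3 and the residual variance is 1 − b². The true variance of the arm estimate divided by the variance the model reports is 1.5 × (1 + 2ρ)/(2 + ρ). Type I error is 2 × [1 − Φ(1.96/√ratio)].

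| ρ | ratio | type I, formula | type I, simulation |
|---|---|---|---|
| 0.3 | 1.043 | 5.5% | 5.5% |
| 0.5 | 1.200 | 7.4% | 7.6% |
| 0.7 | 1.333 | 9.0% | 9.9% |
| 0.85 | 1.421 | 10.0% | 9.9% |

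**Reading B: arm-by-time terms, independent rows.** The month-6 contrast is the arm difference at month 6 minus the arm difference at baseline. The covariate cancels, leaving a comparison of raw changes from baseline.

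- Estimate: no dilution (0.249 to 0.251 in simulation).
- Type I error in simulation: 4.4%, 4.7%, 3.4% and 2.8% at ρ = 0.3, 0.5, 0.7 and 0.85. The ratio of true to reported variance is 9/[4(2 + ρ)], which is below 1 throughout (0.978 at 0.3, 0.789 at 0.85), so the test is conservative.
- Power at ρ = 0.3: the true standard error is √(2/247 × 2 × 0.7) = 0.1065 and the reported one is √(2/247 × 2 × 0.7156) = 0.1076. Power is Φ[(0.25 − 1.96 × 0.1076)/0.1065] = 64%.
- A month-6 analysis of covariance has standard error √(2/247 × (1 − 0.09)) = 0.0858 and power Φ(0.25/0.0858 − 1.96) = 83%.
- The loss narrows as ρ rises: in simulation, 76% against 90% at 0.5, and 92% against 97% at 0.7.

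**Follow-up visits only, baseline as covariate, clustered on patient.** Mean estimate about 0.25 and type I error 5.1% to 5.4%.

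**Outcomes covered.** Ideation has all three measurements. Reattempt has no varying baseline value, because everyone has just attempted. Suicide death has none by nature. Costs and satisfaction are measured once. The rule as worded can be carried out in full only for ideation.

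**The case against.** The strongest reply is that this is a condensed article. It names a model family, and correlation structure and contrasts are commonly left to the full protocol or analysis plan. GEE extends that same family. A reader might infer that the model ignores repeated measures and that its p-values are therefore too small. The text does not support that: it is silent on independence, and under arm-by-time terms the test is conservative even with independent rows. This part of the objection stands, and the type I error figures are conditional.

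A reader might also infer that the main result is at risk. It is not shown to be. The month-6 proportion has its own test, and nothing makes the longitudinal model the primary analysis. An inflation figure for reattempt would need separate month-6 and month-13 rates, and the sample size section gives a single expected rate of 18%.

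It can further be said that the history of suicide attempt, recorded at baseline, is a natural counterpart for reattempt. That is a reasonable covariate, but it is not the baseline value of the same outcome, which is what the rule calls for.

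What the objection does not remove is the double role of baseline. That is written out in two adjacent sentences, so it is not a detail left for elsewhere.

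**Conclusion.** The point holds, at moderate severity. The stated rule makes baseline both a response and a covariate, and both contrasts examined are worse than using it as a covariate alone. An averaged arm effect loses exactly one third of its size when the true effect is read over months 6 and 13 (0.25 SD becomes about 0.17 SD), with or without clustering. Arm-by-time terms avoid this but give up power, about 64% against 83% at an assumed correlation of 0.3 and less of a gap at higher correlations. These figures assume a continuous score, equal correlation between visits, complete data on 247 per arm and an effect of 0.25 SD.

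Type I error of about 6% to 10% arises only if the effect is averaged and visits are also analysed as independent, which the article does not say. It would go too far to claim that estimates are diluted and p-values too small as a settled fact, since the outcome depends on choices left open. The consequence falls mainly on suicidal ideation. The chi-square or Fisher comparison of reattempters at month 6 and the 247 per group are unaffected.

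**What to change.** Reword the paragraph so that month-6 and month-13 values are the only responses and the baseline value is only a covariate. Fit a GEE or mixed model clustered on patient with arm, time and arm-by-time, and name the arm contrast to be tested. Limit adjustment for the baseline value to outcomes that have one, which as described means ideation. If reattempt is modelled, adjust for the history of suicide attempt already recorded at baseline. State that the month-6 chi-square or Fisher test remains the primary comparison.

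The cost is one paragraph of wording, to be settled before the data are unblinded. No new data are needed and the sample size does not change.
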